## Abstract

**Background:**

Frailty is a term commonly used to describe the condition of an older person who has chronic health problems, has lost functional abilities and is likely to deteriorate further. However, despite its common use, only a small number of studies have attempted to define the syndrome of frailty and measure its prevalence. The criteria Fried and colleagues used to define the frailty syndrome will be used in this study (i.e. weight loss, fatigue, decreased grip strength, slow gait speed, and low physical activity). Previous studies have shown that clinical outcomes for frail older people can be improved using multi-factorial interventions such as comprehensive geriatric assessment, and single interventions such as exercise programs or nutritional supplementation, but no interventions have been developed to specifically reverse the syndrome of frailty.

We have developed a multidisciplinary intervention that specifically targets frailty as defined by Fried et al. We aim to establish the effects of this intervention on frailty, mobility, hospitalisation and institutionalisation in frail older people.

**Methods and Design:**

A single centre randomised controlled trial comparing a multidisciplinary intervention with usual care. The intervention will target identified characteristics of frailty, functional limitations, nutritional status, falls risk, psychological issues and management of chronic health conditions. Two hundred and thirty people aged 70 and over who meet the Fried definition of frailty will be recruited from clients of the aged care service of a metropolitan hospital. Participants will be followed for a 12-month period.

**Discussion:**

This research is an important step in the examination of specifically targeted frailty interventions. This project will assess whether an intervention specifically targeting frailty can be implemented, and whether it is effective when compared to usual care. If successful, the study will establish a new approach to the treatment of older people at risk of further functional decline and institutionalisation. The strategies to be examined are readily transferable to routine clinical practice and are applicable broadly in the setting of aged care health services.

**Trial Registration:**

Australian New Zealand Clinical Trails Registry: ACTRN12608000250336.

## Background

Frailty is a term in common use among health care professionals. It is a term often used to label the condition of an older person who has health problems, has lost functional abilities and is likely to deteriorate further. It is thus a syndrome, describing a health state that could occur as the result of a number of underlying health conditions. As a summary term it has some utility, but little practical clinical or scientific value unless it is adequately defined.

Rockwood and colleagues [1] describe the concept of frailty as a 'multidimensional syndrome of loss of reserves (energy, physical ability, cognition, health) that gives rise to vulnerability'. The clinical conceptualisation of frailty has been described as an observable physical and functional decline in the body associated with physiological changes during later life [2], which is accompanied by social and emotional experiences [3]. Clinical research on frailty has enabled the provision of care to the older population to target those most at risk [4] and in need [5], and to allocate appropriate services and resources [6].

However, frailty does not have a precise definition [7] and is not a specific diagnosis [8]. It is seen as an increasingly common condition in older people but is not an inevitable part of ageing. Many older people are not frail and never become frail, and frailty is also observed in younger people. It is not synonymous with disability as many disabled people are not frail. However, frailty results in disability, and it usually indicates a person at increased risk for morbidity and mortality [9,10].

There have been a number of attempts to define frailty. It has been described in terms of a syndrome, characterised by decreased reserve and resistance to stressors, resulting from cumulative declines across multiple physiological systems that are close to or past symptomatic clinical failure [11]. Rockwood [12] proposed that the essential feature of frailty is the notion of risk due to instability. Consequently, the frail person is at increased risk of disability and death. Frailty has been described as a "pre-death" syndrome [13], and it has been shown to be the commonest trajectory at the end of life, and to be associated with stroke, Alzheimer's Disease and other dementias, delirium, Parkinson's Disease, hip fracture, incontinence, pneumonia, dehydration, syncope, lower limb cellulitis [14]. Bortz [8] postulated that frailty is the result of early disease in multiple systems resulting in impaired muscle strength, mobility, balance and endurance. He considered that active intervention should be able to reverse much of the state of frailty. The definition of frailty used in the FICSIT (Frailty and Injuries: Cooperative Studies of Intervention Techniques) trials is also focussed on strength, mobility, balance and endurance [15].

Following the Cardiovascular Health Study, Fried et al [16] formulated specific criteria that defined the frailty syndrome. These criteria offer an empirically derived and validated definition for frailty based on the presence of at least three or more defined characteristics. The presence of frailty, as defined by Fried et al, was shown to be independently predictive over a three year period of incident falls, worsening mobility, deteriorating function in activities of daily living, hospitalisation, and death. The Fried frailty characteristics are unexplained weight loss, muscle weakness, self-reported exhaustion, poor endurance (as demonstrated by slow walking speed) and low activity level.

In a United States community dwelling population, aged over 65 years, Fried et al [16] found that 7% of the population met the criteria for frailty. Prevalence of frailty increased with each five-year cohort, and was double in women compared to men. After analysis of data from 2762 older people, Fried et al [16] described three separate aspects of functioning: frailty, disability and co-morbidity. Of people who were frail, 73% concurrently experienced one or both of the other conditions.

Attempts have been made to improve clinical outcomes for frail older people, however no interventions have been developed to specifically reverse the syndrome of frailty. Previous intervention studies targeting frail older people have focussed on using general interventions such as comprehensive geriatric assessment [17-19] and rehabilitation models [20], with inconclusive effects on functional ability and well-being. A recent systematic review found community-based, multifactorial interventions reduce hospital admission in the frail population, but do not significantly benefit physical function in this group [21]. Specific interventions targeting physical activity have been shown to improve physical function [22,23], and intervention with nutritional supplements plus exercise has resulted in increased energy intake [23]. Pharmacological interventions [24-26] produced inconsistent results.

Major limitations of the intervention studies targeting frail older people include the absence of an agreed definition for the term 'frailty'which would allow the precise identification of appropriate patients [2], and the lack of combined intervention studies that evaluate individual needs and customise care to promote the development of function and quality of life in frail older people [21].

Many clients of aged care health services are frail. This study seeks to establish whether a multifactorial, multidisciplinary intervention specifically targeting frailty can be implemented in a general metropolitan hospital aged care service setting, and whether it is effective when compared with usual care.

We are seeking to establish the effect of the intervention on both frailty and mobility. Specifically the hypotheses are that the multifactorial, multidisciplinary intervention will improve performance on a frailty index score and on a mobility index score calculated from the Short Physical Performance Battery score. The secondary outcome measures include days of hospitalisation and residence in nursing care facilities, risk of falling, additional measures of mobility, depression and quality of life. In addition, the study will test whether the Fried definition of frailty can be applied readily in a clinical setting and the ability of an aged care health service to effectively provide the intervention.

If this frailty intervention is shown to be effective, there are major potential benefits to the frail older population generally in terms of decreased disability. Significant cost savings could flow to government and broader society if hospitalisation or institutionalisation can be avoided or postponed. The interventions being examined are readily transferable to routine clinical practice and can potentially be applied routinely in aged care services.

## Methods and Design

### Design Outline

A single centre randomised controlled trial with a 12-month follow-up period will be conducted among 230 frail older persons (see Figure 1). A multidisciplinary intervention that targets identified characteristics of frailty will be compared with usual care. At the study site, usual care for non-institutionalised frail older people involves the General Practitioner (GP), community services and some home visiting programs to provide therapy.

**Figure 1 F1:**
[figure not shown]
**Overview of the flow of participants through the Frailty Intervention Trial**. Adapted from the CONSORT diagram [27,28].

### Recruitment and Eligibility

Eligible participants will be identified from older people (men and women aged 70 years or more) seen by clinicians working with the Division of Rehabilitation and Aged Care Services (DRACS) at Hornsby Ku-ring-gai Health Service (in urban northern Sydney, Australia). DRACS is a large clinical service that has programs operating in the community and in the hospital setting, and incorporates an Aged Care Assessment Team. Eligible participants will have completed their treatment program before being approached to enter the study. Once a person agrees to participate in the study informed consent will be sought, and if granted, the study nurse will screen for inclusion criteria.

The inclusion criteria are: adults aged 70 years or older with 3 or more of the Fried Frailty Criteria [16]; not usually living in a residential aged care facility; residing in the Hornsby or Ku-ring-gai local government areas (in Sydney, Australia); without severe cognitive impairment (defined as a Mini Mental State Examination (MMSE) score of 18 or less); not an ongoing client of DRACS and without an illness likely to be associated with a life expectancy of less than 12 months. People who do not meet all of the inclusion criteria or who do not consent will not be included. Residents of nursing care facilities are excluded from the study because one of the outcomes of interest is residence in a nursing care facility.

Participants satisfying the inclusion criteria will be individually randomised to either usual care from their general practitioner and community services, or to an individualised intervention designed to treat the identified components of frailty.

The Northern Sydney & Central Coast Health Human Research Ethics Committee has approved the study protocol – Research Protocol Number 0709-191M.

### Measurements and Procedures

Baseline measures will be assessed prior to randomisation. Outcomes will be assessed at three and twelve months by a researcher who has been blinded to group allocation. Participants will receive monthly calendars at the baseline assessment, with instructions to record the following events: falls; home visits by community services, nursing and allied health personnel; general practitioner appointments; use of hospital transport; receipt of delivered meals; hospitalisations and admissions to nursing care facilities. Participants will be asked to post the completed calendar to the blinded research personnel monthly. Telephone contact will be made with the participant if the calendar is not received, is completed incorrectly, or a fall, hospitalisation or admission to a nursing care facility, has occurred.

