### Treatment Allocation

#### Randomisation

Permuted block randomisation is used to achieve balanced treatment allocation [47]. A set of permuted blocks was generated for each of two strata ('frail' with 3 frailty criteria and 'very frail' with 4 or 5 frailty criteria). A random number sequence was generated for the order of treatment allocation within the blocks using the SPSS v15 RV.UNIFORM function. Varying block sizes were used. The blocks were randomly arranged within larger sized blocks. Random group allocation will be managed by project personnel not involved in measurement or intervention. The treatment allocation tables for both strata will be stored centrally off site.

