#### Allocation Concealment

Enrolment of participants will be managed by the Research Consultant who will screen for inclusion criteria, seek informed consent and conduct the baseline assessment. Following completion of baseline assessment, the Research Consultant will telephone the central study office; the participant will be assigned a participant number and allocated to the intervention or control group. Staff performing the outcome assessment and data analysis will be blinded to group allocation but it is not possible to blind participants and staff administering interventions to group allocation.

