The effectiveness of exercise in the frail population is documented [22,23,57,58]. The WEBB program was chosen to deliver the exercise as it incorporates the findings of previous studies [50] as well as a recent systematic review of exercise for falls prevention (Sherrington et al., manuscript under review). Adequate intensity of exercise will be ensured by fortnightly physiotherapy home visits in the initial three months. Five visits over the subsequent nine months will enable review of the program, in light of the complex comorbidities in this population. Further, nutritional intervention in undernourished older adults has been found to increase weight and decrease mortality [59]. In frail people, nutritional supplementation has been found to increase total energy intake when used in conjunction with exercise [23].

Multiple steps have been taken to maximise adherence to the intervention. There will be a flexible time-frame for the intervention, goal setting, the involvement of family/carers, treatment in the home environment and the assessment of factors known to contribute to exercise adherence.

Applying the Fried frailty criteria in a clinical setting is not equivalent to the context in which these criteria were developed. An epidemiological study, retrospectively applying the frailty criteria to a cohort of community-dwelling adults 65 years and older, examining the prevalence of frailty and correlating frailty status with factors such as falls and hospitalisation, is clearly different to a clinical trial. It is our impression that some older people have difficulty answering the self report questions that define three of the five Fried criteria (unexplained weight loss, self-reported exhaustion, and low physical activity), and also that cognitive impairment compounds these difficulties. Other studies have since modified the original physical activity criterion [32,60] because of difficulty using the questions in the initial Fried study. The criterion used by Cesari and colleagues [32] has been adapted to fit the timeframe of this study.

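### Monthly calendars that record home therapy visits are posted to blinded staff, which puts assessor blinding at serious risk

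*Protocol article*

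**What the plan says.** Measurements and Procedures promises a blinded assessor: "Outcomes will be assessed at three and twelve months by a researcher who has been blinded to group allocation". Allocation Concealment repeats this and adds the analysts: "Staff performing the outcome assessment and data analysis will be blinded to group allocation". It accepts that participants and treating staff cannot be blinded.

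The same Measurements and Procedures section sets up a monthly calendar. Besides falls, GP appointments and hospital transport, its entries include "home visits by community services, nursing and allied health personnel" and "receipt of delivered meals; hospitalisations and admissions to nursing care facilities". On return of the form: "Participants will be asked to post the completed calendar to the blinded research personnel monthly". The section then provides for calls: "Telephone contact will be made with the participant if the calendar is not received, is completed incorrectly, or a fall, hospitalisation or admission". The last of these events means entry to residential care. Under Secondary outcomes, each recorded fall leads to a telephone interview in which the researcher establishes its circumstances and any injury.

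The Intervention section gives home physiotherapy, capped at ten sessions over the year, to anyone with weak grip, slow walking or low activity. It also allows home-delivered meals to be recommended to those who meet the weight loss criterion. The Discussion gives the timing: "Adequate intensity of exercise will be ensured by fortnightly physiotherapy home visits in the initial three months", followed by five visits in the remaining nine months.

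**The concern.** Some of the calendar entries are contacts that the intervention itself produces. Staff whom the protocol wants kept blind are thus sent, every month, a partial record of treatment delivery, and the first ones arrive before the first outcome assessment. This comes from a procedure the protocol states, not from a detail that a short article has left out.

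Assessor blinding matters here because participants know their arm. The frailty outcome includes exhaustion and activity items collected by interview. Grip, timed walk and chair rise are standardised but depend on effort, which an assessor's encouragement can influence. Classifying a fall is itself outcome assessment, and it is done in conversation with an unblinded participant by someone who may have the service-use entries in hand.

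**Working it through.** The protocol gives no figure on this point to reproduce. The check has three steps.

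**1. Who qualifies for home physiotherapy?** Entry requires at least three of five Fried criteria (Recruitment and Eligibility). Three criteria trigger physiotherapy: weakness, slow walking and low activity. Two do not: weight loss and exhaustion. The number of eligible profiles is C(5,3) + C(5,4) + C(5,5) = 10 + 5 + 1 = 16. A profile without a trigger could hold at most two criteria, so none is eligible. All 16 of 16 profiles qualify.

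**2. How much is on the forms before the 3-month assessment?** The cap of ten sessions less the five later visits leaves 10 − 5 = 5. A strict fortnightly count over 13 weeks gives 13/2 = 6.5, or about six. Six plus five is 11, which exceeds the cap, so I use about five; the argument is the same with six. Calendars for months 1 and 2 should be in hand by the 3-month visit. The third covers the month that ends at about that visit. Two or three calendars will therefore have been returned.

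**3. How informative are they?** Let q1 and q0 be the shares of intervention and control participants whose calendars show repeated home allied health visits. With equal allocation, and a reader who guesses intervention whenever such a pattern appears:

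- share of intervention guesses that are right = q1 / (q1 + q0)
- share of all guesses that are right = (q1 + 1 − q0) / 2

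The documents give neither q1 nor q0. I assume q1 from 0.85 to 1.0 and q0 from 0.05 to 0.50. The lower value of q1 matches the 15% non-compliance allowed for under Sample Size. The range for q0 is wide because usual care includes some home therapy at an unstated rate.

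| q1 | q0 | Intervention guesses right | All guesses right |
|---|---|---|---|
| 0.85 | 0.05 | 0.944 | 0.900 |
| 0.85 | 0.20 | 0.810 | 0.825 |
| 0.85 | 0.50 | 0.630 | 0.675 |
| 1.00 | 0.05 | 0.952 | 0.975 |
| 1.00 | 0.20 | 0.833 | 0.900 |
| 1.00 | 0.50 | 0.667 | 0.750 |

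An intervention guess is right 63% to 95% of the time, and all guesses together 68% to 98%, against 50% by chance. By the second formula the pattern carries no information only if q0 equals q1, that is, if controls show repeated home visits as often as intervention participants do.

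**The case against.** A reader might infer that the blind is broken outright, and that the arm can be read off for nearly every participant before month 3. The documents do not support that, for these reasons.

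- **Overlap of staff is not stated.** The article speaks of a blinded researcher for the assessments and of blinded personnel for the calendars. It does not say that they are the same people. This stands. It does not remove the concern, because the only staff Allocation Concealment names as blinded are outcome assessors and analysts, and because the fall interview is outcome assessment whoever does the 3- and 12-month visits.
- **Control calendars can carry similar entries.** Design Outline says usual care includes some home therapy programs. This stands, so an entry does not prove allocation. Recruitment and Eligibility weakens it: participants have finished their treatment and are not ongoing clients of the service, so repeated home therapy soon after entry is less likely in controls.
- **Delivery will not be complete.** The sample size allows for dropout and non-compliance, and the Discussion describes flexible timing. This stands and is the reason for letting q1 fall below 1.
- **Some outcomes have other protection.** Under Secondary outcomes, hospital and facility admissions are confirmed from records, so they are less exposed. Mobility is timed and has no interview item. Exhaustion and activity are reported by unblinded participants, a source of bias that assessor blinding cannot remove. All of this narrows the concern but leaves fall classification, and assessor influence on effort and interview items, within it.

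**Conclusion.** The concern holds as a serious risk to blinding, not as proof that blinding fails. The stated procedure sends staff who are meant to stay blinded a monthly record that includes the intervention's own home visits. Every intervention participant qualifies for those visits, and about five fall before the 3-month assessment.

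On the assumed rates the forms raise correct guesses from 50% to between 68% and 98%. That range rests on assumptions about q1 and q0 and on equal allocation; the step that every participant qualifies rests on the protocol alone.

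The exposure is clearest for the classification of falls by telephone. It reaches both primary outcomes only if those who see the calendars also do the 3- and 12-month assessments, which the article neither states nor rules out. Hospital and facility admissions are better protected.

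**What to change.** Split the calendar into two parts with separate return addresses.

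- **Events** (falls, hospitalisations, facility admissions) go to the blinded staff, who make the event calls.
- **Service use** (home visits, GP appointments, transport, meals) goes to existing project staff outside measurement. The Randomisation section shows that such staff exist: "Random group allocation will be managed by project personnel not involved in measurement or intervention". Calls about a missing or faulty service-use part should come from them.

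State in the protocol that anyone who sees service-use data does no 3- or 12-month assessment and no event call. Record the assessors' guess of allocation, so that the success of blinding can be reported.

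Redirecting the whole calendar to the staff who manage allocation would be simpler but is not sound: falls data would then be received by unblinded staff whom the protocol keeps out of measurement.

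The cost is a two-part form, one line of procedure and a small clerical load. The split does not stop a participant from disclosing visits during a call; the recorded guesses would help to show how far that happens. Recruitment began in January 2008, so the change should be made before further assessments, because one made with a compromised blind cannot be repaired later.
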